#### 4.4. Food producers

The food products will be produced by GC Rieber Compact, a private Norwegian company created in 1948 and with extensive experience in among other things developing and producing nutritional products for the prevention and treatment of malnutrition. The nutritional supplementation products has been developed in collaboration with the University of Copenhagen and technical advisors from WFP and GC Rieber Compact based on the position paper from WHO on the composition of foods for children with MAM. The 12 food supplements all contain the same micronutrient composition but differ in the amount of fat, protein, quality of soy and percentage of protein provided by DSM. A detailed description of the composition of the different products can be found in annex 2.

The shelf life of iCSBs and LNS is 9 and 24 months respectively. Shipment of food supplements to the project site will take shelf life into account.

GC Rieber Compact has not been involved in the design of the study, nor will they be involved in the analysis and interpretation of the data.

A supply agreement has been made between GC Rieber Compact, MSF Denmark and University of Copenhagen for the development, production and future use of the nutritional supplementation products developed for this study. This agreement ensures that results of this study are placed in the public domain, meaning that any producer, not only GC Rieber Compact, are free to produce the final products.

#### 4.5. Commitment of ALIMA to use the results of the trial and sustainability of the intervention

At the end of the trial, ALIMA is willing to use the most relevant strategy for the management of MAM identified through the trial as part of its nutritional activities in Burkina Faso and other countries. The results of this study would be communicated to and benefit the beneficiaries of UN agencies and NGOs involved in the management of childhood acute malnutrition.

#### 4.6. Collaborative partnership

The trial's sponsor is Department of Nutrition, Sports and Exercise, University of Copenhagen in a research collaboration with Médecins sans Frontières Denmark. This proposal was developed following advice of technical referents on trial design, conduct, and analysis, composed of leading experts in nutrition. All investigators in this study are financially independent from this study and no conflicts of interest are reported.

It is a strong wish to involve researchers from the Institut de Recherche en Science de la Santé, Burkina Faso well as to collaborate with the nutrition department of the Ministry of Health. The exact nature of the collaboration with the IRSS is currently being elaborated. So far staff from the IRSS have been involved in the project one of which will be supported to do a PhD. as

#### 4.7. Financing and Insurance

The trial is funded by Danida and MSF-Norway. Insurance has been taken with HDI-Gerling Industrie Versicherung which is a Europe-based accredited company. The insurance covers 1848 children (including children recruited for the pilot) and covers indemnification against all sums that the Study sponsor should become legally liable to pay, namely damages resulting from bodily injury arising from the Study up to 2 years after completion of the Study. See separate insurance policy in annex 14.

#### 4.8 Communications

The study results will be communicated in Burkina Faso (written report and oral presentation) to the health authorities of Burkina Faso and to the community of Province de Passoré, involved in the study.

Publications will be written with the input of all co-investigators and supervisory staff and submitted to international peer-reviewed journals.

## 5. Study schedule and training

. Training of the field team will be ensured by ALIMA and the PhD students of the University of Copenhagen involved in the project. In addition, all partners will ensure regular support. During the study, continuous supervision, regular meetings and reporting will ensure updating of knowledge and permanent training throughout the study.

Recruitment of the children is expected to begin in August 2013 and last for 6 months (Table 3). For each child, the intervention is scheduled for three months, with an additional three months of follow-up of all children participating in the trial. In total, the study is expected to last for one year including follow-up period.

**Table 3 Study schedule**

| Year      |                          | 2013 |   |   |   |   |   |   |   |   |    |    |    | 2014 |   |   |   |   |   |   |   |   |
|-----------|--------------------------|------|---|---|---|---|---|---|---|---|----|----|----|------|---|---|---|---|---|---|---|---|
| Month     |                          | 1    | 2 | 3 | 4 | 5 | 6 | 7 | 8 | 9 | 10 | 11 | 12 | 1    | 2 | 3 | 4 | 5 | 6 | 7 | 8 | 9 |
| Pre-study | Pilots                   | X    | X |   |   |   |   |   |   |   |    |    |    |      |   |   |   |   |   |   |   |   |
|           | Adjustments after pilots |      |   | X | X | X |   |   |   |   |    |    |    |      |   |   |   |   |   |   |   |   |
| Study     | Inclusion                |      |   |   |   |   |   |   | X | X | X  | X  | X  | X    |   |   |   |   |   |   |   |   |
|           | Supplementation          |      |   |   |   |   |   |   | X | X | X  | X  | X  | X    | X | X | X |   |   |   |   |   |
|           | Follow-up                |      |   |   |   |   |   |   |   |   |    | X  | X  | X    | X | X | X | X | X | X |   |   |

### **Summary of changes to the protocol:**

A protocol, version 50, had received ethical approval from the ethics committee in Burkina Faso in November 2012. Upon approval, a pilot study was carried out January-March 2013. Following completion of the pilot, minor technical changes in methods were introduced in the protocol such as a fixed three hours equilibration time for the diluted deuterium technique. Also, there was a change of scientific sponsor. Therefore, version 52 attached above is therefore the original, as well as the final approved, protocol sent to Ethics Committee with no subsequent amendments.

### **Summary of changes to the statistical analysis plan:**

Compared to the statistical plan outlined in the protocol, we eventually decided to deviate on two issues:

1) Our primary outcome was fat-free mass accretion over three months, adjusted for length. We have not changed the primary outcome, but decided to do the length adjustment by dividing with length in meters squared, ie expressing fat-free mass accretion as an index. There are several reasons for this: First, we found that dividing by length in meters squared was the optimal adjustment. Second, since children are growing in length, then it is not enough to adjust for baseline length. Using fat-free mass index at both time points enable us to adjust for not only baseline length, but also changes in length over time.

2) We had initially planned to adjust for multiplicity, in case we had to compare 12 groups. However, while this reduces the risk of type 1 errors, it also increases the risk of type 2 errors. We therefore eventually followed standard practice of not adjusting p-values for reduced factorial model. In other words, for the pairwise comparisons within factors in the reduced models no multiplicity adjustments were applied.

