### 3.1.5. Outcomes and adverse events

#### **Efficacy**

- Primary outcome: absolute lean-mass increment (in kg) from baseline at 3 months using deuterium dilution technique.
- Secondary outcomes lean-mass increments in kg/cm and in g/kg/day, increase of WHZ to >-2, linear growth, MUAC, level of physical activity, development in motor and language milestones, thymic size, morbidity (e.g. malaria, severe anemia, severe acute malnutrition, diarrhea, respiratory infection, hospitalization, death), hemoglobin concentration, serum acute phase proteins, IGF-1, serum ferritin and whole blood concentrations of essential fatty acids.

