### 3.1.13. *Data analysis*

The main effectiveness criterion will be the mean change in lean body mass after 3 months of supplementation (absolute increase expressed in kg). The primary analysis will be conducted in the intention to treat (ITT) population and will therefore include all randomized subjects having at least one exploitable baseline and 3 months LBM measures,. The primary analysis will be conducted by means of a single statistical analysis including both main arms, ie LNS and iCSB:

- A three-way analysis of variance (ANOVA) will be used to evaluate if the two interventions modify the effect of dehulled soy and soy isolate at different levels of milk content.
- The ANOVA will also include LBM at baseline as well as a number of additional explanatory (age, sex, MUAC, WHZ, season) that adjust for potential differences present in the study population. To adjust for variation between centers random effects for each centre are also included in the model. Thus, the statistical model will be based on a linear mixed model.
- Pairwise comparisons of means within and across the two arms will be done using the linear mixed model. Multiplicity will be taken into account by adjusting all pairwise comparisons.
- The effect of supplementation, ie. the difference in mean changes in LBM at 3 months of each group will be presented in terms of estimated means with 95% confidence intervals.

All other statistical analyses of the primary endpoint, ie other study populations, sub-group analysis, and inside-the-table comparisons, and all statistical analyses of secondary endpoints, will be considered secondary analyses. These include:

- Evaluation of the effect of the type of soy by comparing, in the LNS and the iCSBs groups separately, the mean increase in LBM at 3 months over the two groups of soy quality (dehulled soy i.e. 3 groups merged, soy isolate i.e. 3 groups merged).
- Evaluation of the effect of the milk protein content by comparing, in the LNS and the iCSBs groups separately, the mean increase in LBM at 3 months over the three groups of milk protein content (i.e. 2 groups merged for each level of milk).
- Analysis might also be conducted among the subgroup of participants presenting these 2 LBM measurements and the per-protocol population (i.e. excluding participants with violation of protocol).

For all secondary analyses, no adjustment for multiplicity is planned.

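### The adopted primary analysis replaces the kg lean-mass increment with a length-squared index that uses post-randomisation length, yet says the outcome is unchanged

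*Combined protocol and SAP*

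**What the plan says.** Section 3.1.5 (Efficacy) sets the primary outcome as "absolute lean-mass increment (in kg) from baseline at 3 months using deuterium dilution technique". Section 3.1.13 repeats it as the main criterion: "mean change in lean body mass after 3 months of supplementation (absolute increase expressed in kg"). The Outcomes paragraph of the protocol summary also calls it an absolute increment. The primary model in section 3.1.13 adjusts for baseline LBM and for "age, sex, MUAC, WHZ, season", with a random centre effect. Length is not named.

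The protocol did consider scaling by length, but as a secondary outcome and per centimetre. Section 3.1.5 lists "lean-mass increments in kg/cm and in g/kg/day, increase of WHZ to >-2, linear growth" among the secondary outcomes, so linear growth is an efficacy outcome too.

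Item 1 of the Summary of changes to the statistical analysis plan describes the analysis finally adopted. It states that the primary outcome was already length-adjusted and is unchanged, and that the authors "decided to do the length adjustment by dividing with length in meters squared, ie expressing fat-free mass accretion as an index". It gives two reasons. The first is that "we found that dividing by length in meters squared was the optimal adjustment". The second is that children grow during the trial, so taking the index at both visits also accounts for growth after baseline.

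**The concern.** There are two separate problems.

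The first is the record. A reader of item 1 would believe that the protocol's primary outcome was length-adjusted and that only the form of adjustment moved. Sections 3.1.5 and 3.1.13 show a kg increment with no length term, so the primary outcome did change.

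The second is what the new outcome measures. Month-3 length is observed after randomisation and the products may affect it. Dividing by its square removes any part of the lean-mass effect that comes with extra growth. The primary objective in section 2.2 is the increase in lean body mass, and the sample size in section 3.1.7 is built on that increase. The index answers a different question: lean mass relative to body size. If a product adds both tissue and length, the two outcomes can rank products differently.

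**Working it through.** **The plan's own figure.** Section 3.1.7 uses n = 16·s²/d² with d = 0.4 SD: 16/0.4² = 100 per cell. Allowing for 25% loss, 100/0.75 = 133.3, rounded up to 134, and 12 × 134 = 1608. This reproduces exactly. It is sized on the change in lean body mass. The documents give no SD in kg or in kg/m², so power on the index scale cannot be derived from them.

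**General rule.** Let F and L be the reference group's month-3 fat-free mass and length, d a product's extra lean mass in kg, and x its extra length. With equal baselines, the difference in index change is

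(F + d)/(L + x)² − F/L²

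It is zero when x = L·(√(1 + d/F) − 1). Because 1.01² = 1.0201, 1% more length needs about 2% more lean mass to break even. This holds for any body size.

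**Inputs for an illustration (assumptions, not in the documents).**
- Reference gain over 3 months: 0.85 kg and 3.5 cm.
- Baselines: 5.0 kg/66 cm, 6.0 kg/70 cm and 7.5 kg/78 cm of fat-free mass and length.
- Benefit d: 0.10 to 0.24 kg, which is 0.4 SD if the SD of the change lies between 0.25 and 0.6 kg.

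**One case in full (6.0 kg/70 cm, d = 0.10 kg).**
- Baseline index: 6.0/0.70² = 12.245.
- Reference at month 3: 6.85/0.735² = 12.680.
- Product, no extra length: 6.95/0.735² = 12.865, an advantage of 0.185 kg/m².
- Product, 0.25 cm extra: 6.95/0.7375² = 12.778, an advantage of 0.098.
- Product, 0.5 cm extra: 6.95/0.740² = 12.692, an advantage of 0.012.
- Break-even: 73.5 × (√(1 + 0.10/6.85) − 1) = 0.53 cm. Beyond that the sign reverses.

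**Across the assumed range.** The last two columns give the share of the kg benefit still visible on the index after 0.5 cm of extra growth.

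| Baseline | Break-even, d = 0.10 kg | Break-even, d = 0.24 kg | Kept at 0.5 cm, d = 0.10 | Kept at 0.5 cm, d = 0.24 |
|---|---|---|---|---|
| 5.0 kg/66 cm | 0.59 cm | 1.41 cm | 15% | 64% |
| 6.0 kg/70 cm | 0.53 cm | 1.28 cm | 6% | 60% |
| 7.5 kg/78 cm | 0.49 cm | 1.16 cm | −3% | 56% |

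The size of the benefit matters more than the size of the child. The near-total loss at 0.5 cm belongs to the smallest assumed benefit.

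**The case against.** A fat-free mass index is a legitimate measure, and lean mass relative to size is a coherent question in children enrolled partly on weight-for-height. Linear growth has its own result, so a growth benefit would not go unseen. The index is openly listed as a deviation, with reasons. All of this stands. It supports reporting the index, but not treating it as the protocol's primary outcome.

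It can also be said that a difference between a summary of changes and the protocol is not in itself an error. That is right, and the point does not rest on the difference alone. Item 1 describes the analysis actually adopted. What is wrong is its account of the protocol outcome and its use of month-3 length.

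A reader might go further and infer that the scale was picked to suit the result, so that pre-specification is void. The documents do not show that. Item 1 says the exponent was found to be optimal but gives no dataset, date or criterion. A pilot had already tested length and deuterium measurement (section 3.1.11), and an exponent can be chosen without looking at arms. Section 3.1.8 keeps product codes sealed until after the primary analysis, which limits selection by result if the choice was made while coded. What remains is non-disclosure, and masking does not undo the adjustment for a post-randomisation variable.

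A reader might also infer that the protocol expects milk to increase length. Section 1.1 offers that only tentatively, as a possibility of interest.

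**Conclusion.** The point holds. The primary outcome was changed from a kg increment to change in fat-free mass over length squared, and the statement that it is unchanged is inaccurate. The index can shrink, cancel or reverse a product's lean-mass benefit when that product also increases length, at about 2% of lean mass for each 1% of length. Under the assumed benefits and baselines, break-even lies at roughly 0.5 to 1.4 cm of extra growth over three months.

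The documents give no between-product difference in length gain, so the actual loss is unknown, and nothing here shows that any product's ranking was in fact altered. Nor do they say that the kg result will go unreported; they are silent on it. Because the problem lies in the primary outcome, it should be corrected before the primary conclusion is drawn.

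**What to change.** - Keep the kg increment as the primary outcome and base the primary conclusion on it. Add baseline length as a covariate alongside baseline LBM. This deals with differences in starting size without using anything measured after randomisation.
- Report the change in index as a secondary analysis, labelled as not pre-specified, next to the length-gain result so the two can be read together.
- State when, from which data, by what criterion and under what masking the exponent was chosen.
- Delete the sentence saying that the primary outcome has not changed, and correct the one saying it was already length-adjusted.

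The cost is one model rerun and revised wording. Baseline length is already collected, no new data are needed, and the sample size stays at 1608.
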